**Methods/design:**

This ongoing study is a single-blind, single-center, parallel group, randomized controlled trial. Sixty-two participants will be recruited from Shanghai Shuguang Hospital and randomized into either the EA group or the sham EA group. Baihui, Sishencong, Ganshu, Sanyinjiao, and Taichong are selected as the treatment acupoints in both groups. The EA group will receive the traditional EA treatment with de-qi sensation, and the sham EA group will receive sham EA treatment without needle penetration and electrostimulation. Participants will receive treatment 3 times per week for a total of 12 sessions over 4 weeks. The primary outcome is Hamilton Rating Scale for Depression score, and the secondary outcomes are scores on the Zung Self-Rating Depression Scale, National Institutes of Health Stroke Scale, Barthel Index of Activities of Daily Living, and Depression Scale of traditional Chinese medicine. All of the outcome measures will be assessed at baseline, 2 weeks after EA treatment onset, 4 weeks after treatment onset, and at 8-week follow-up. Safety assessments will be done at each visit.

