### Sample size

According to the difference of HRSD scores between the two groups, the required sample size of each group will be carefully calculated by the data statistician. Based on our previous pilot study, the change in the SD of HRSD scores in the sham EA group is 5 points and that in the EA group is 13 points. If the HRSD score change in the EA group is 8.5 points higher than that in the sham EA group, it will be considered clinically significant. On the basis of a 5% false-positive error rate (α = 0.05, two-sided) and 80% power (β = 0.2), the sample size is estimated as follows:$$ {\displaystyle \begin{array}{l}n=\frac{{\left({Z}_{1-\alpha }+{Z}_{1-\beta}\right)}^2\times \left({\sigma}_1^2+{\sigma}_2^2\right)}{\delta^2}\\ {}\kern1.5em =\frac{{\left(1.96+1.28\right)}^2\times \left({5}^2+{13}^2\right)}{8.5^2}\approx 28.48\end{array}} $$

A sample size of at least 29 participants should be recruited in each group. Assuming about a 10% dropout rate, which has been verified in the pilot study, a total of 62 participants will be enrolled in the trial.

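### Enrolling 62 with about 10% dropout leaves about 28 per group, one below the stated minimum of 29; the declared 80% power is not at risk

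*Protocol article*

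**What the plan says.** The Sample size section gives the whole calculation. On variability it says that "the change in the SD of HRSD scores in the sham EA group is 5 points and that in the EA group is 13 points". The target difference follows: "If the HRSD score change in the EA group is 8.5 points higher than that in the sham EA group". The text declares a two-sided α of 0.05 and 80% power, and the printed formula uses the quantiles 1.96 and 1.28 and ends at about 28.48.

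The section then concludes: "A sample size of at least 29 participants should be recruited in each group". The next sentence brings in attrition: "Assuming about a 10% dropout rate, which has been verified in the pilot study, a total of 62 participants will be enrolled". How 29 per group becomes 62 in total is not shown.

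The Abstract repeats the total ("Sixty-two participants will be recruited from Shanghai Shuguang Hospital"), and Recruitment strategies gives the same target. Randomization and allocation fixes a 1:1 ratio, so 62 means 31 per group.

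**The concern.** A dropout allowance exists so that the required number remains once the expected losses have occurred. Here the required number, the expected loss and the enrolled total stand in adjacent sentences, and the third does not follow from the first two. A reader of the eventual trial report will take it that 62 was chosen to secure 29 per group at 10% attrition. It does not do so.

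At stake is the accuracy of the published sample size justification. If the gap were large, the power claimed for completers would be at stake too, so its size has to be checked.

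**Working it through.** **Inputs** (all from Sample size, except the allocation ratio): SDs 5 and 13, read here as SDs of the HRSD change; difference 8.5; two-sided α 0.05; declared power 80%; printed quantiles 1.96 and 1.28; minimum 29 per group; dropout about 10%; total 62; ratio 1:1.

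**1. The plan's own n per group.** n = (z₁ + z₂)² × (σ₁² + σ₂²) / δ².
- With the printed numbers: (1.96 + 1.28)² × (25 + 169) / 8.5² = 10.4976 × 194 / 72.25 = 28.19.
- The protocol prints 28.48, a small slip. Both round up to 29, so the minimum of 29 is reproduced.

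**2. What 62 delivers at 10% dropout.**
- 62 × 0.9 = 55.8 in total, or 31 × 0.9 = 27.9 per group. Rounded: 56 completers, 28 per group.
- The minimum is 2 × 29 = 58.

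**3. The dropout that 62 can absorb.** 1 − 58/62 = 4/62 = 6.5%. As an add-on to 58, the four extra patients are 4/58 = 6.9%. Neither figure is about 10%.

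**4. What 29 per group after 10% loss would need.** 29/0.9 = 32.2, so 33 per group and 66 in total. Rounding on the total instead, 58/0.9 = 64.4, so 65.

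**5. Possible origins of 62.**

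| Starting n per group | × 1.1, per group | ÷ 0.9, per group |
|---|---|---|
| 28.19 (recomputed) | 31.0 | 31.3 |
| 28.48 (printed) | 31.3 | 31.6 |
| 29 (stated minimum) | 31.9 | 32.2 |

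An unrounded n of 28.19 or 28.48, inflated either way and rounded down, gives 31 per group and 62 in total. Starting from the stated 29, multiplying by 1.1 and rounding up gives 32 per group (64), and dividing by 0.9 gives 33 per group (66).

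**6. Power for 8.5 points.** Normal approximation: Φ(8.5 / √(194/n) − 1.96). The second column uses the noncentral t with Welch degrees of freedom (34.8 at n = 28, 36.1 at n = 29).

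| n per group | Normal | Welch t |
|---|---|---|
| 28 | 89.8% | 88.1% |
| 29 | 90.8% | 89.2% |

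For n = 28: √(194/28) = 2.632; 8.5/2.632 = 3.229; 3.229 − 1.96 = 1.269; Φ(1.269) = 0.898.

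**7. The same formula at the declared 80%.** With 0.84 in place of 1.28, n = 21.1, so 22 per group. Then 22/0.9 = 24.4, so 25 per group and 50 in total. At 22 per group the normal approximation gives 81.7% and the Welch t 78.8%.

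**The case against.** Four things can be said for the plan.

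- **The word recruited.** Taken literally, the minimum of 29 is a recruitment figure, and 31 per group satisfies it. This does not stand. The next sentence adds a dropout allowance and raises the total above 58, so 29 has to be the number meant to remain.
- **About 10% is loose.** Retaining 28 of 31 is a 9.7% loss, and the gap is one patient per group. The smallness is conceded. The looseness does not close the gap, because 29 per group survives only a loss of 6.5% or less.
- **Completers are not the analysis set.** Statistical analysis plans an ITT analysis with maximum likelihood for the primary outcome, which is measured at several time points. Patients who leave early can still contribute partial data. This stands: 28 per group counts completers and is not simply the ITT set. It bears more directly on the per-protocol analysis.
- **No declared property is lost.** The only power declared is 80%, and 28 per group exceeds it. This also stands.

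A reader might draw two stronger conclusions. The first is that the authors multiplied by 1.1 where they should have divided by 0.9. The protocol does not show its inflation step. Division by 0.9 applied to an unrounded n also leads to 62, while multiplying the stated 29 by 1.1 leads to 64, so the documents do not identify the cause. The second is that the trial is underpowered. That would follow only if 90% were the declared target. Even then the normal-approximation shortfall is 0.2 percentage points, and the Welch figure is below 90% with the full 29 per group, so dropout is not what causes it.

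**Conclusion.** The inconsistency is real and can be checked within one section: the stated enrolment does not leave the stated minimum at the stated dropout. The shortfall is about one completer per group, or 3 to 4 enrolled patients against a full 10% allowance. It costs about one percentage point of power and leaves the declared 80% untouched.

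The larger problem in the same section is that the declared 80% disagrees with the 1.28 in the formula. The minimum of 29 depends on that quantile, so the dropout figures cannot be judged properly until the intended power is stated.

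The power figures assume SDs of 5 and 13 for the change score, a true difference of 8.5 points, equal groups, and a comparison of completers at a single time point.

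**What to change.** Keep 62 and rewrite the justification so that its figures agree. For example: 62 patients will be enrolled (31 per group); with about 10% dropout, about 28 per group are expected to complete, which gives about 88–90% power for a difference of 8.5 points under SDs of 5 and 13. Alternatively, keep 29 per group and state that 62 allows for 6.5% dropout.

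In the same edit:
- State the intended power and make the formula match it. If 80% is intended, replace 1.28 with 0.84 and report 22 per group, noting that 62 exceeds the 50 this requires. If 90% is intended, correct the declared power and β.
- Correct 28.48 to the value that the formula gives (28.19 with the printed quantiles).
- Show the inflation step as n/(1 − dropout).

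The cost is wording only. Enrolment, randomization and conduct are unchanged. A total of 66 would be needed only if the sponsor chose to hold 29 completers per group after a 10% loss, and the declared 80% power does not require that.

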### Data collection, management, and monitoring

The case report form and adverse events form will be carefully checked and input into the computer by two independent researchers to ensure data accuracy. All the original forms will be archived in the clinical research center of Shanghai Shuguang Hospital. The study will be monitored monthly by the data and safety monitoring board (DSMB) of the clinical evaluation center of Shanghai Shuguang Hospital, which will make the final decision to terminate the trial if any serious acupuncture-related AE occurs. The data manager of the DSMB can have access to the final dataset and has the right to give approval to others who need to gain access to the final dataset.

### Statistical analysis

An independent statistician will use IBM SPSS Statistics 24.0 software to conduct the whole data analysis. According to the intention-to-treat (ITT) principle, both ITT and per-protocol (PP) analyses will be performed. Any participant who receives treatment more than nine times during the study will be enrolled in the PP analysis. In terms of ITT analysis of secondary outcomes, the last observation carried forward rule will be used as the strategy in management of missing data. For the primary outcome, the maximum likelihood estimation method will be used.

All continuous variables will be presented as mean ± SD, and categorical variables will be presented as number (percent). The statistical significance level is considered to be 0.05 (two-sided) with 95% CIs. The homogeneity of the baseline characteristics between the two groups is designed to be tested by the two-sample *t* test for quantitative data and the chi-square test for qualitative data. If there is a possibility of covariance, analysis of covariance (ANCOVA) will be used for adjustment of baseline characteristics. To compare variables between the two groups, the parametric two-sample *t* test for normally distributed data and the nonparametric Mann-Whitney *U* test for nonnormally distributed data will be used. Repeated-measures ANCOVA will be applied to analyze different time point assessments between groups and interaction between groups and observed time. Differences within groups will be assessed with the paired *t* test (parametric method) and the Wilcoxon signed-rank test (nonparametric method).

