## Methods/design

### Hypotheses

Patients with PSD with 12 sessions (4 weeks) of EA treatment will have certain improvements in their symptoms and QoL scores.Patients with PSD treated with EA will experience alleviation of their symptoms and have increased QoL scores significantly greater than those treated by sham EA.

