#### Primary outcome

The changes in HRSD scores between baseline, 2 weeks after EA treatment onset, 4 weeks after treatment onset, and at 8-week follow-up will be set as the primary outcome of the clinical study.

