#### Secondary outcomes

Secondary outcomes include the Zung Self-Rating Depression Scale (SDS), National Institutes of Health Stroke Scale (NIHSS), Barthel Index of Activities of Daily Living (BI), and Depression Scale of traditional Chinese medicine (Depression Scale of TCM), all of which will be evaluated at the same time points as the assessment of the primary outcome.

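### Last observation carried forward is the only ITT rule for the secondary scales, although patients are expected to improve; a likelihood-based repeated-measures model should replace it

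*Protocol article*

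**What the plan says.** The Statistical analysis section of the protocol article sets two missing-data rules. For the ITT analysis of secondary outcomes, "the last observation carried forward rule will be used as the strategy in management of missing data". For the HRSD, "For the primary outcome, the maximum likelihood estimation method will be used". No sensitivity analysis accompanies the first rule, and no model is named for the second.

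The Secondary outcomes section lists SDS, NIHSS, Barthel Index and the Depression Scale of TCM, "all of which will be evaluated at the same time points as the assessment of the primary outcome". The Primary outcome section gives those time points: "The changes in HRSD scores between baseline, 2 weeks after EA treatment onset, 4 weeks after treatment onset, and at 8-week follow-up".

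The between-group methods are "the parametric two-sample *t* test for normally distributed data", with Mann-Whitney as the nonparametric alternative, and ANCOVA for baseline adjustment. For the longitudinal comparison, "Repeated-measures ANCOVA will be applied to analyze different time point assessments between groups and interaction between groups and observed time". The software is SPSS 24.0.

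Change over time is expected. The Hypotheses section states that patients given "EA treatment will have certain improvements in their symptoms and QoL scores". The Interventions section gives both groups basic Western medical therapy for stroke, and the Recruitment strategies section says that participants will mainly be inpatients. The Sample size section assumes about 10% dropout and does not split it by arm.

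**The concern.** LOCF assumes that a patient's score stops changing on the day of the last visit. That sits badly with a treated stroke population in which NIHSS and Barthel Index may improve in both arms through recovery and standard care. A patient who leaves after baseline or week 2 is scored at follow-up as if no further recovery took place.

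Three consequences follow:

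- Change within each arm is understated.
- A real difference between arms is pulled towards zero when dropout is equal.
- A difference appears where none exists when one arm loses more patients, or loses them earlier. Its direction depends on which arm that is.

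Unequal loss is plausible here. The Dropout criteria section counts as dropouts patients who take other treatment for their depression and patients who do not complete the treatment schedule. Either could occur more often in one arm. LOCF's error depends on that imbalance.

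**Working it through.** **Inputs from the protocol article.** 62 patients randomised 1:1, so 31 per arm; about 10% dropout; assessments at baseline, week 2, week 4 and 8-week follow-up; two-sided 5% level. The article gives no figure for the effect of LOCF, so there is none to reproduce.

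**Assumed inputs (not in the article).** The size of recovery on a Barthel-like scale, SD 15, correlation 0.7 between visits, and the split of dropout between arms.

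**Step 1. Formula.** If a share d of an arm drops out and an average improvement R is still to come, LOCF lowers that arm's mean change by d × R. The bias in the EA minus sham difference is therefore

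bias = −(d_EA × R_EA − d_sham × R_sham).

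**Step 2. No true effect, total recovery of 10 in both arms.** The full 10 is lost if dropout follows baseline. Half of it, 5, is lost if dropout follows week 2 and half the recovery is still to come.

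| Dropout EA / sham | After week 2 (R = 5) | After baseline (R = 10) |
|---|---|---|
| 10% / 10% | 0 | 0 |
| 15% / 5% | −0.5 | −1.0 |
| 5% / 15% | +0.5 | +1.0 |

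At 10% / 10% the difference is unbiased, but each arm's recovery is still understated by 0.5 to 1.0 points.

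**Step 3. True difference of 5 (recovery 15 on EA, 10 on sham).**

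- 10% / 10%: after baseline, 15 × 0.90 − 10 × 0.90 = 4.5; after week 2, 15 × 0.95 − 10 × 0.95 = 4.75.
- 15% / 5%: after baseline, 15 × 0.85 − 10 × 0.95 = 3.25; after week 2, 15 × 0.925 − 10 × 0.975 = 4.12.
- 5% / 15%: after baseline, 15 × 0.95 − 10 × 0.85 = 5.75; after week 2, 15 × 0.975 − 10 × 0.925 = 5.38.

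**Step 4. Effect on the test.** Null simulation: 31 per arm, SD 15, correlation 0.7, dropout after week 2, two-sample *t* test on the follow-up score. Here the stated gain is all still to come after week 2. The formula gives the expected bias: −(0.15 − 0.05) × 10 = −1.0 and −(0.20 − 0.05) × 15 = −2.25.

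| Dropout EA / sham | Later gain | Mean false difference | Rejection |
|---|---|---|---|
| 10% / 10% | 10 | 0 | about 5% |
| 15% / 5% | 10 | about −1.0 | 5.5% to 6% |
| 20% / 5% | 15 | about −2.2 | about 8.5% |

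The *t* test's estimated standard error was close to the empirical one (3.99 against 4.00 in the last row). The excess rejection therefore comes from the shift in means.

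**Step 5. Why the HRSD belongs in the remedy.** A separate illustrative HRSD simulation used a true difference of 8.5 and mean dropout of 14.7%, with EA patients more likely to leave after a poor early response. Mean estimates were 8.53 by maximum likelihood, 9.19 on complete cases and 6.85 by LOCF. The gain from the stated rule for the HRSD is realised only if the between-group analysis itself is likelihood-based.

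**The case against.** The strongest reply is that the harm is conditional. The article gives one overall dropout figure of about 10%. With equal dropout and no treatment effect, LOCF leaves the between-group comparison unbiased and the test at its nominal level. At an average of 10%, even a threefold imbalance (15% against 5%) moves test size only slightly. The 8.5% case needs 12.5% average dropout and a large late gain. Only secondary outcomes are affected. All of this stands, and it limits the size of the point. It does not rescue the rule, because equal dropout still shrinks a true effect and nothing in the plan would show a reader how much LOCF matters.

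Three stronger readings are tempting, and the documents do not support them:

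- **That the maximum likelihood commitment for the HRSD is not delivered.** A reader might infer this because the listed tests are often run on complete cases, and might then count about 10% of 62, or 6 patients, as lost from the primary analysis. The article names SPSS but no procedure. A repeated-measures ANCOVA with group, time and their interaction can be fitted by maximum likelihood as a mixed model, and maximum likelihood could also be used to impute first. Listwise deletion is not stated.
- **That LOCF makes the standard errors too small here.** In the simulation the estimated and empirical values nearly agree.
- **That the two rules contradict each other.** Each is explicitly assigned to its own outcomes. Using both is inconsistent practice, not a contradiction.

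**Conclusion.** The point holds for the secondary outcomes. The plan fixes LOCF as their only ITT rule in a setting where scores are expected to move. Following it as written understates change within arms, shrinks a true difference (5 points to between 4.5 and 4.75 at 10% dropout per arm) and can create a false difference of either sign when dropout is unequal. On the assumed Barthel-like scale that false difference is about 1 point at 15% against 5%, and about 2.2 points in the more extreme case. It is zero when dropout and recovery are equal.

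These sizes rest on assumed recovery, SD, correlation and dropout splits; only the sample size and the overall 10% come from the article. For the HRSD the stated handling is sound in principle. What is needed there is a named model, so that the handling is not lost if the repeated-measures ANCOVA were run on complete cases only. This is worth correcting, but it does not threaten the primary conclusion.

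**What to change.** Replace LOCF for SDS, NIHSS, Barthel Index and the Depression Scale of TCM by a likelihood-based mixed model for repeated measures. It should include baseline value, group, visit and group-by-visit, use all observed post-baseline visits, and take the between-group contrast from the model. Keep LOCF at most as a labelled sensitivity analysis. Name the same model for the HRSD, in place of or as the definition of the repeated-measures ANCOVA, so that all scales rest on one missing-data assumption.

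The cost is a change of wording in the analysis section. SPSS MIXED is part of the software already named, no new data are needed, and recruitment was still under way when the article was written. The price in assumptions is reliance on missingness at random, which should be stated. Reporting dropout by arm and visit would let readers judge it.

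### No baseline-HRSD-adjusted comparison is fixed in advance: adjustment and choice of test depend on the data, at a cost mainly in precision, and no unequal-variance method is named despite planned SDs of 5 and 13

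*Protocol article*

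**What the plan says.** The Statistical analysis section of the protocol article sets out these steps.

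- Baseline comparison: "The homogeneity of the baseline characteristics between the two groups is designed to be tested by the two-sample" *t* test for quantitative data, and by the chi-square test for qualitative data.
- Adjustment: "If there is a possibility of covariance, analysis of covariance (ANCOVA) will be used for adjustment of baseline characteristics". Neither the condition nor the characteristics are specified.
- Between-group test: "To compare variables between the two groups, the parametric two-sample" *t* test if the data are normal, and the Mann-Whitney *U* test if they are not.
- Longitudinal analysis: a repeated-measures ANCOVA for group differences across time points and for the group-by-time interaction. It carries no condition, but its covariate is not named.
- Missing data: maximum likelihood for the primary outcome.

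The Primary outcome section defines the outcome as HRSD change across baseline, 2 weeks, 4 weeks and the 8-week follow-up. The inclusion criteria admit HRSD scores from 8 to 35. The Sample size section states that "the change in the SD of HRSD scores in the sham EA group is 5 points and that in the EA group is 13 points" and uses a formula with a separate variance for each arm. The Statistical analysis section does not mention an unequal-variance method.

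**The concern.** Two printed rules let the data choose the analysis. In a randomised trial a baseline difference is chance, so a baseline significance test does not show whether adjustment is worthwhile. What matters is how strongly the baseline variable predicts the outcome. Baseline HRSD is the obvious candidate when the outcome is HRSD change and entry scores range widely. If adjustment waits for a signal of imbalance, most trials forgo the precision that baseline HRSD could give, and a moderate imbalance that misses significance stays in the estimate.

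The normality check likewise switches the analysis between a comparison of means, on which the trial is sized, and a rank test that does not target means. The planned SDs differ by a factor of 2.6 (13/5), and with unequal spread neither the pooled t test nor Mann-Whitney reliably keeps its nominal level for a comparison of means. The repeated-measures ANCOVA stands beside these rules without being named as the analysis that decides the trial.

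**Working it through.** **Inputs from the protocol article.** Change SDs 5 (sham) and 13 (EA); difference 8.5 points; two-sided 5% level; 1:1 allocation; 62 enrolled (31 per arm); about 10% dropout, so 62 × 0.9 = 55.8, or 28 per arm.

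**The plan's own figure.** (1.96 + 1.28)² × (5² + 13²)/8.5² = 10.4976 × 194/72.25 = 28.19. The article prints 28.48; both round up to 29 per group. The value 1.28 belongs to 90% power although the text says 80%. That is a separate matter, but it explains why the powers below are near 90%.

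**Assumptions not in the article.** The correlation ρ between baseline HRSD and HRSD change is set at -0.2, -0.4 or -0.6. The adjustment trigger is modelled as baseline p < 0.05 and the normality trigger as Shapiro-Wilk p < 0.05, because neither is defined.

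**Precision.** The unadjusted SE at 31 per arm is √(194/31) = 2.50. Take ρ equal in both arms and a common slope of 9ρ per baseline SD, where 9 = (5 + 13)/2. The two residual variances then sum to 194 − 162ρ². This gives √(187.52/31) = 2.46, √(168.08/31) = 2.33 and √(135.68/31) = 2.09 for the three correlations. Simulated values for fixed adjustment are 2.47, 2.34 and 2.11, which agree. Fixed adjustment is compared with the conditional rule below (10,000 null trials at 31 per arm; 5,000 power trials at 28 per arm).

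| ρ | SE fixed / conditional | Power fixed / conditional | Type I error fixed / conditional |
|---|---|---|---|
| -0.2 | 2.47 / 2.48 | 89% / 89% | 5.1% / 5.0% |
| -0.4 | 2.34 / 2.44 | 93% / 90% | 5.0% / 4.7% |
| -0.6 | 2.11 / 2.40 | 96% / 90% | 5.2% / 4.1% |

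The gain in SE runs from almost nothing to (2.40 − 2.11)/2.40 = 12%.

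**Unequal spread.** Rejection rate under equal means, SDs 5 and 13, normal data, 20,000 trials:

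| Sham / EA analysed | Pooled t | Welch | Mann-Whitney |
|---|---|---|---|
| 31 / 31 | 5.3% | 5.1% | 6.4% |
| 28 / 28 | 5.4% | 5.2% | 6.5% |
| 31 / 25 | 7.3% | 5.1% | 7.5% |
| 25 / 31 | 3.8% | 5.1% | 5.6% |

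Repeat simulations put the pooled test at 25/31 between 3.4% and 3.8%.

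**Normality switch.** With skewed (gamma) errors and these SDs, Mann-Whitney rejects equal means in 8.8-17.4% of trials and the pretest-then-choose rule in 7.9-17.2%. With equal SDs the pretest rule gives 4.7-5.1%, so the excess comes from the unequal spread and not from pretesting itself.

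**The case against.** The strongest reply is that the longitudinal model is already planned. The repeated-measures ANCOVA carries no condition, maximum likelihood is specified for the primary outcome, and together they suit an outcome measured at several visits. A full analysis plan, not shown here, could name the covariate. This stands to the extent that most of the remedy is already in the text. It does not cancel the printed conditional rules, and nothing says which analysis prevails.

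Four stronger readings are tempting, and the documents do not support them.

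- *The plan uses equal-variance tests.* The article says only two-sample t test, without pooled or Welch, and its sample-size formula allows unequal variances. With equal arms even the pooled form holds about 5%. The 31/25 split is one direction of a possible imbalance; the reverse split makes the test conservative.
- *Conditional adjustment inflates the false-positive rate.* Over all trials it gives about 4-5%. A rate of 7-12% can be produced at assumed baseline-to-follow-up correlations of 0.4-0.7, but only for an unadjusted test of the follow-up score, and only within the roughly 14% of trials whose baseline gap exceeds 0.35 SD yet is not significant. Trials with smaller gaps reject at 2-4%.
- *Omitting ANCOVA costs 33% or 54% in variance.* Those figures come from 2/(1 + r) at r = 0.5 and 0.3, which needs equal variances at baseline and follow-up. That conflicts with change SDs of 5 and 13. With those SDs and an assumed common baseline SD of 3-5.5, the saving is about 0-7% at r = 0.3, 0-4% at r = 0.5 and 8-27% at r = 0.7.
- *Adjustment depends on a baseline p value.* The phrase about a possibility of covariance could also mean a relation with the outcome. The p < 0.05 trigger is a modelling choice made here.

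**Conclusion.** The concern holds in this limited form. The article prints data-dependent rules for adjustment and for the choice of test, and it does not fix a comparison adjusted for baseline HRSD. The repeated-measures ANCOVA does not settle this, because its covariate and its standing as primary are both unstated.

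The cost of conditional adjustment is mainly precision: 0 to 12% of the SE and 0 to 6 percentage points of power, for assumed baseline-change correlations of -0.2 to -0.6. Overall type I error is not raised, although an individual trial with a moderate, non-significant imbalance would go uncorrected. Power under the conditional rule stays at 89-90%, above the stated 80%, so the trial is not underpowered on this account.

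The unequal-spread issue is separate and conditional. It matters if the t test is the pooled form and the arms end up unequal (about 7% or 3.5% at 31 against 25), or if Mann-Whitney is read as a test of means (about 6.5% with equal arms, more with skewed data). The plan should be changed, but the point does not invalidate the design.

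**What to change.** Make the likelihood-based repeated-measures model already foreshadowed in the Statistical analysis section the single primary analysis of HRSD change. Include group, visit, group-by-visit and baseline HRSD in every case, allow group-specific variances, and name the contrast that serves as the primary result. ANCOVA with heteroscedasticity-robust standard errors is an acceptable alternative. With HC3 errors and normal data it gave 4.5-4.7% type I error and 88%, 92% and 96% power at the three assumed correlations.

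Remove baseline significance tests as a trigger for adjustment; a descriptive baseline table is enough. Remove the normality switch and keep Mann-Whitney as a sensitivity analysis. Where a two-sample t test remains, state that it is the Welch form.

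The cost is a change of wording before the data are unblinded, plus a check that the planned software fits the chosen variance structure. It needs no new data, visits or patients.
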